## Abstract

Responsive infant feeding is a key strategy for childhood obesity prevention. Responsive feeding involves caregivers responding to infant hunger and satiety cues in a timely and developmentally appropriate manner. There is a dearth of evidence-based information and guidance for caregivers on how to responsively feed their infants. The aim of this research is to co-design a Reusable Learning Object (RLO) and guidance infographic to improve caregiver awareness, understanding and use of responsive infant feeding behaviours. The Capability, Opportunity, Motivation and Behaviour (COM-B) model of behaviour change and the Aim, Storyboarding, Populate specification, Implement media, Review and release prototype, and Evaluate (ASPIRE) approach for digital intervention co-design will be utilised. Four co-design workshops with caregivers of infants and healthcare professionals (HCPs) will determine priority RLO content. Content analysis will enable RLO development and process reporting. Formative and summative surveys will be conducted to evaluate the usability of the RLO, its impact on caregivers and its potential implementation into NHS care pathways. The output will be a RLO on responsive feeding for caregivers and an infographic for HCPs/support workers which will contribute to a future obesity prevention intervention. The findings will be disseminated to stakeholders and submitted for publication in a peer-reviewed journal.

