##### Recruitment for Evaluation

We will conduct a preliminary evaluation of the functionality, acceptability and usability of the RLO. Caregivers, HCPs and support workers (who were not part of the RLO development) will be recruited for either a formative survey or one of two summative surveys. Potential participants will be emailed a link to the RLO, patient information sheet (PIS), informed consent form (ICF) and respective survey. Participants will be given up to two weeks to access and complete the surveys and will be able to work through the RLO as many times as they require during this two-week period.

Survey 1—Up to 20 caregivers, HCPs and support workers will be asked to review the prototype RLO for content and ease of use.

Survey 2—Up to 30 caregivers will be recruited via Small Steps Big Changes (https://www.smallstepsbigchanges.org.uk/) and public contributors.

Survey 3—Up to 30 HCPs and support workers will be recruited via contacts at the Institute of Health Visiting and the Royal College of Midwives and gatekeepers at local NHS trusts who will be asked to send the survey via email to HCPs and support workers.

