*Survey 1* (formative) responses will explore the usability of the RLO content and functionality and will be completed by caregivers, HCPs and support workers. The questions have been adapted from a survey tool by Johnson et al. exploring the usability of an e-learning resource to improve the knowledge and confidence of teachers working with children born pre-term [35]. Survey 1 (see Appendix A Table A1 survey A1) will consist of 9 closed questions with responses of agree, neutral or disagree to questions such as “the CRIB-RLO resource held my interest”.*Survey 2* (summative) (see Appendix A Table A2 survey A2) will be completed by caregivers and will ascertain the impact of the RLO on caregivers in terms of changing behaviours related to responsive feeding. There will be 7 closed questions on a 3-point scale from agree, neutral and disagree, including questions such as “The CRIB-RLO resource has improved my confidence in knowing how to feed my baby” and “The CRIB-RLO resource has increased my motivation to actively look for and respond to my babies cues during feeding”.*Survey 3* (summative) (see Appendix A Table A3 survey A3) will be completed by HCPs working with caregivers of infants and will explore the implementation of the RLO and infographic in practice within the NHS and other organisations. The questions have been developed based on a the Theoretical Framework of Acceptability (TFA) developed by Sekhon et al. [36]. The TFA can be used to evaluate the prospective and retrospective acceptability of healthcare interventions by both intervention deliverers and intervention participants. Preliminary reliability testing on the Sekhon et al. TFA adapted for examining the implementation of a telephone-assisted coaching framework revealed three main factors. These are affective attitude and effectiveness (Cronbach’s alpha 0.9, coherence and understanding (0.77), perceived burden (0.85), and suggesting an appropriate level of internal consistency for each construct [37].

Survey 3 will include a mixture of eight open and two closed questions on the implementation of the RLO in practice. Open questions include those such as “Can you describe any additional effort you might need to employ to implement the CRIB-RLO/Infographic into practice?” and closed questions such as “how prepared are you to deliver the CRIB RLO to caregivers?” with a 5-point Likert scale ranging from not at all prepared to highly prepared.

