##### Analysis

Survey responses will be downloaded to an Excel/Sav file.

Survey 1 responses evaluating RLO content, functionality and usability will be analysed with descriptive statistics in the form of frequencies and percentages. The data will be categorised to highlight areas of function or content that require amending.Survey 2 responses examining the impact and usefulness of the RLO on caregivers will be analysed with frequency tables and descriptive statistics. Data from the closed questions will be analysed to examine the impact of the RLO on changing behaviours related to responsive feeding.Survey 3 responses from HCPs exploring the implementation of the RLO and infographic will be a mixture of quantitative and qualitative data. The quantitative data from the two Likert scale questions will be analysed with frequency tables and descriptive statistics. The qualitative data gathered from the open questions will be analysed using content analysis [34].

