## 4. Discussion

Whilst population-based approaches are needed to address the multiple and complex causes of childhood obesity, individual prevention efforts that support parents with infant feeding make a useful contribution. There is strong evidence that individual obesity prevention interventions delivered during early life that promote and support responsive feeding result in healthier weight trajectories for infants [15]. However, there is no universal information and support focused on responsive feeding; thus, there is a need to improve information for caregivers who feed infants and the HCPs who work with them. This study will co-produce a RLO for caregivers of infants to increase awareness, understanding and use of responsive infant feeding behaviours. In addition, we will developed infographic guidance for HCPs and support workers to use with caregivers alongside the RLO.

This research will been conducted in a comprehensive, systematic and evidence-based way by applying the MRC framework for complex interventions [23], the COM-B model and the ASPIRE approach [29]. This will help to ensure that the developed RLO and infographic responsive feeding outputs are robust and acceptable to both caregivers of infants and the HCPs working with them.

The co-design and initial evaluation of the RLO and infographic will allow for future testing of the intervention effectiveness on both responsive feeding behaviours and child weight outcomes within a randomised control trial. Providing improved support for responsive feeding for caregivers and HCPs who work with them has the potential to reduce non-responsive feeding practices such as overfeeding, which can lead to obesity.

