## Appendix A

**Table A1 healthcare-12-00029-t0A1:** Survey A1: Usability of the CRIB-RLO.

Part 1 The CRIB-RLO resource ^1^ *Please indicate the extent to which you Agree, are Neutral or Disagree, with the following statements*		
The CRIB-RLO resource held my interest.		
Agree	Neutral	Disagree
2. I enjoyed using the CRIB-RLO resource.		
Agree	Neutral	Disagree
3. I found the CRIB-RLO resource easy to use.		
Agree	Neutral	Disagree
4. The visual elements added to my understanding of the topic.		
Agree	Neutral	Disagree
5. The audio commentaries were engaging.		
Agree	Neutral	Disagree
6. The case studies were engaging.		
Agree	Neutral	Disagree
7. I would prefer to use the CRIB-RLO resource than read written information.		
Agree	Neutral	Disagree
8. It was clear from the learning objectives what was in each section.		
Agree	Neutral	Disagree
9. I would recommend the CRIB-RLO resource to other caregivers or healthcare professionals/support workers.		
Agree	Neutral	Disagree
10. If you Disagree with any of the above statements, please add your suggestions for improving this resource?		
Final Version 1.1, 04/07/2023, IRAS 326807, FMHS 238 0323		

^1^ Questions derived from a survey tool used by: Johnson, S.; Bamber, D.; Bountziouka, V.; Clayton, S.; Cragg, L.; Gilmore, C.; Griffiths, R.; Marlow, N.; Simms, V.; Wharrad, H.J. Improving developmental and educational support for children born preterm: Evaluation of an e-learning resource for education professionals. *BMJ Open*
**2019**, *9*, e029720. https://doi.org/10.1136/bmjopen-2019-029720 [35].

**Table A2 healthcare-12-00029-t0A2:** Survey A2: Impact on caregivers.

Part 1 You			
Please indicate if you are a caregiver or a member of the CRIB public contributors group?			
*Please tick the box*			
Caregiver			
Public contributor			
If you are a caregiver, do you have a child less than one year old?			
Yes			
No			
2. Were you involved in the development of the CRIB-RLO resource?			
Yes			
No			
3. If you would like a link to the final resource please provide your email address below			
Part 2 Your learning			
*Please indicate the extent to which you Agree, are Neutral or Disagree, with the following statements*			
The CRIB-RLO resource has improved my understanding of when my baby is hungry and when they are full.			
Agree	Neutral	Disagree	
2. I am more likely to feed my baby based on their cues or signs than other ways for example, other people’s advice.			
Agree	Neutral	Disagree	

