3. I am more likely to feed my baby based on their cues or signs than other ways such as instructions on baby food tins.			
Agree	Neutral	Disagree	
4. The CRIB-RLO resource has improved my confidence in knowing **how** to feed my baby.			
Agree	Neutral	Disagree	
5. The CRIB-RLO resource has improved my confidence in knowing **when** to feed my baby.			
Agree	Neutral	Disagree	
6. The CRIB-RLO resource has helped me understand when it might be more difficult to read my babies signs and cues.			
Agree	Neutral	Disagree	
7. The CRIB e-learning resource has increased my motivation to actively look for and respond to my babies cues during feeding.			
Agree	Neutral	Disagree	

**Table A3 healthcare-12-00029-t0A3:** Survey A3: HCPs implementation into NHS/other organisations.

Part 1 You					
1. Please indicate your main area of work?					
					*Please tick the box*
Health visitor					
Parent support worker					
Midwife					
Children’s Nurse					
Nursery Nurse					
Breastfeeding or lactation consultant					
Other, please state					
2. Please indicate your employing organisation?					
Nottinghamshire Healthcare NHS					
Nottingham City Care Social Enterprise					
United Hospitals Lincoln					
Local Authority					
Charity or NGO					
Higher Education					
Other, please state					
3. Were you involved in the development of the CRIB-RLO resource?					
Yes					
No					
4. If you would like a link to the final resource please provide your email address below					
Part 2 Please provide your views on the CRIB-RLO and the Infographic ^1^					
Please indicate how you feel about the CRIB-RLO and Infographic?					
2. Can you describe any additional effort **you** might need to employ to implement the CRIB-RLO/Infographic into practice?					
3. Is the CRIB-RLO/Infographic a good fit with your own values around how you give infant feeding advice? Please describe any areas where there is conflict.					
4. Do you understand the information contained in the CRIB-RLO/Infographic?					
5. Do you think the CRIB-RLO/Infographic work well together as a way of improving caregiver responsive feeding?					
6. What aspects of the process of providing infant feeding advice in your team/organisation might alter as a result of caregivers having access to the CRIB-RLO?					
7. On a scale of 1-5 how effective do you think the CRIB intervention will be in changing the way caregivers feed their infants?					

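### Survey 2 cannot report satiety separately from hunger, because item 1 combines the two and no item asks about knowing when to stop a feed

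*Protocol article*

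**What the plan says.** The Abstract defines the target behaviour by two kinds of cue: "Responsive feeding involves caregivers responding to infant hunger and satiety cues in a timely and developmentally appropriate manner". The Introduction repeats this definition and links overfeeding in the first year to rapid weight gain. The Discussion says that better support for responsive feeding "has the potential to reduce non-responsive feeding practices such as overfeeding, which can lead to obesity".

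The Method part of Section 2.3.4 says that Survey 2 "will ascertain the impact of the RLO on caregivers in terms of changing behaviours related to responsive feeding", and describes its format: "There will be 7 closed questions on a 3-point scale from agree, neutral and disagree". On sample size, Recruitment for Evaluation says "Up to 30 caregivers will be recruited via Small Steps Big Changes". On analysis, which is by frequency tables and descriptive statistics, the plan says: "Data from the closed questions will be analysed to examine the impact of the RLO on changing behaviours related to responsive feeding".

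Table A2, Part 2 prints the instrument. Item 1 reads "The CRIB-RLO resource has improved my understanding of when my baby is hungry and when they are full". Items 4 and 5 ask about improved confidence in knowing how, and knowing when, "to feed my baby". Items 2, 3, 6 and 7 refer to cues or signs without saying which kind.

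**The concern.** Item 1 is double-barrelled: it asks about two things and accepts one answer. A caregiver who learned to read hunger but not fullness, or the reverse, has to choose a response without knowing which part counts. No other item gives fullness on its own, and none asks about recognising the end of a feed.

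Satiety is half of the protocol's own definition and is the half closest to overfeeding. The initial evaluation is meant to prepare for a randomised trial on feeding behaviours and child weight. A favourable frequency on item 1 would not tell the team whether understanding of fullness had improved. Part 2 of Survey 2 has no open-text question through which a respondent could explain, whereas Survey 1 has one and Survey 3 has several. The surveys are described as anonymous, so the plan offers no way to clarify an answer afterwards.

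**Working it through.** The plan gives no figure to reproduce: Section 2.1 states that there is no quantitative hypothesis testing and that no sample size calculation was done. The check is a content count of Table A2, Part 2, followed by bounds on what item 1 can say about fullness.

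**Content count**

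- Item 1: understanding of hunger and fullness, one answer for both.
- Items 2 and 3: likelihood of feeding by cues or signs rather than by other people's advice (2) or tin instructions (3). Kind of cue not stated.
- Item 4: confidence in how to feed.
- Item 5: confidence in when to feed.
- Item 6: understanding of when signs and cues are harder to read. Kind not stated.
- Item 7: motivation to look for and respond to cues during feeding. Kind not stated.

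The seven items match the count in the Method text. Items naming fullness: 1 of 7. Items on fullness alone: 0 of 7. Items on when to feed: 1 of 7. Items on when to stop: 0 of 7.

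**From an observed answer back to fullness**

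Let *n* be the number of respondents, *a* the number who agree with item 1, and *f* the number whose understanding of fullness improved. Take *n* = 30 (the stated maximum) and, as an assumption, *a* = 24 (24/30 = 80%).

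- If respondents agree only when both parts improved, everyone who agrees has gained on fullness, and others may have too: *a*/*n* ≤ *f*/*n* ≤ 1, so 80% to 100%.
- If respondents agree when either part improved, only those who agree can have gained on fullness, and possibly none of them did: 0 ≤ *f*/*n* ≤ *a*/*n*, so 0% to 80%.

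The answering rule is unknown, so item 1 alone leaves the fullness share anywhere from 0% to 100%.

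**From assumed learning forward to the answer**

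Let *h* be the number who gained on hunger. The number agreeing with item 1 lies

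- under the both rule, between max(0, *h* + *f* − *n*) and min(*h*, *f*);
- under the either rule, between max(*h*, *f*) and min(*n*, *h* + *f*).

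With *n* = 30:

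- *h* = 27, *f* = 12: both rule 9 to 12, or 30% to 40%; either rule 27 to 30, or 90% to 100%.
- *h* = 24, *f* = 15: both rule 9 to 15, or 30% to 50%; either rule 24 to 30, or 80% to 100%.
- *h* = *f* = 24, in the same people: both rules give 24/30 = 80%.

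The first two splits are assumptions chosen to show the mechanism. The third shows that the ambiguity vanishes when the two gains coincide. With item 1 as worded, the data cannot show which case applies.

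**The case against.** A reader might infer that Survey 2 can show nothing about satiety. The documents do not support that. Item 1 names fullness. Items 2, 3 and 7 ask about feeding by, or responding to, cues, and the protocol defines the relevant cues as hunger and satiety cues. Item 7 concerns cues during a feed, which naturally include those that it should end. Item 3 sets cues against tin instructions, and the Introduction says that formula companies' volume recommendations compete with parents' reading of cues, so item 3 bears on how much is fed. All of this stands. None of it yields a separate satiety result: items 2 and 3 can be met by starting feeds on hunger cues alone, and item 7 measures motivation, not recognition.

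A reader might also infer that satiety responsiveness is the protocol's route to preventing overfeeding. That goes beyond the text, which credits responsive feeding as a whole and names overfeeding as an example.

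The survey's modest role is a fair defence too. The evaluation is preliminary, the stated objective concerns acceptability, and effectiveness is left to a later trial. Table 1 treats hunger and fullness cues as one topic, which item 1 mirrors. Finding content to amend is mainly the job of Survey 1. A caregiver who gained on only one part could reasonably tick Neutral. Even with item 1 split, the result would be two self-reports after use, not a demonstrated effect. These points keep the matter small. They do not remove it, because the Method and Analysis text still gives these items the task of examining impact on responsive feeding behaviours, and in a descriptive survey the item wording decides what can be concluded.

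**Conclusion.** The point holds as a limit on interpretation. Survey 2 touches on satiety in items 1, 2, 3 and 7 but cannot isolate it, and an Agree frequency on item 1 does not show whether understanding of fullness improved. The content count rests on the printed instrument and needs no assumption. The percentages are illustrations: they assume 30 respondents, hypothetical splits and two extreme answering rules, and they show what is possible, not what is likely. If the gains on hunger and fullness largely coincide, the practical loss is small. No hypothesis test or sample size is affected. This is a cheap improvement, worth making before the survey is sent out.

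**What to change.** In Table A2, Part 2:

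- Replace item 1 with two items of the same form, one on understanding 'when my baby is hungry' and one on understanding 'when my baby is full'.
- Add an item parallel to item 5 on improved confidence in 'knowing when to stop a feed'.
- In the Method text of Section 2.3.4, change the number of closed questions in Survey 2 from 7 to 9 (7 − 1 + 2 + 1 = 9).
- In the Analysis text, state that the hunger and fullness items are tabulated separately.

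This follows the authors' own practice of separating how from when in items 4 and 5. The cost is two extra tick-box items for each respondent and a minor amendment to the survey form.

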The aetiology of childhood obesity is complex. Childhood obesity is linked with the infant feeding environment and in turn, what and how caregivers feed their infants is influenced by their socioeconomic status [5]. Overfeeding within an infant’s first year of life can lead to rapid weight gain, which is the largest risk factor for childhood obesity and overweight [6]. Formula feeding leads to a higher risk of rapid weight gain, regardless of socioeconomic status or extent of breastfeeding [7,8]. Lower maternal sensitivity to infant cues has been associated with rapid weight gain in 6–12-month olds [9]. Infants have been shown to have healthier weight gain trajectories when their caregivers are more responsive to their feeding cues [10]. Responsive parenting forms the basis of attachment between caregivers and infants and is essential for healthy socioemotional development and relationships [11]. Responsive feeding is the reciprocal relationship between infants giving clear hunger and satiety cues and their caregivers responding to these feeding cues promptly and in a developmentally appropriate way [12]. Such supportive early interactions with caregivers can enhance self-regulation, resulting in feeding autonomy and regulatory capacity in infants [13]. There are obesity prevention initiatives and interventions globally that focus on responsive feeding. The US INSIGHT study which delivered a responsive parenting intervention [14] showed reduced use of non-responsive feeding practices such as pressuring an infant to finish a bottle when compared to a control home safety intervention. Interventions delivered at an individual level, where responsive feeding is promoted and supported by healthcare professionals (HCPs), have shown larger improvements for both feeding and weight outcomes than interventions that do not focus on responsive feeding [15]. The World Health Organization (WHO) recommends [16] exclusive breastfeeding for the first six months followed by the introduction of nutritionally adequate and safe complementary (solid) foods. Breastfeeding is a preventative strategy for obesity but many families have negative experiences [17] and/or choose to use formula or combination feed (breast and formula milk). Formula milk companies provide recommendations about the volume of milk to offer an infant relative to their weight but this often vies with parents’ reading of infant cues [18]. Internationally, there are some sources of information for caregivers about responsive feeding. An example is the UNICEF information sheet on responsive feeding [19]; however, this largely focuses on responsive breastfeeding. The American Academy of Paediatrics also have a responsive feeding infographic [20]. However, existing resources do not appear to have been developed using a systematic approach addressing caregiver behaviours and the physical, social, cultural and environmental context [21], nor developed with caregivers.

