Barriers and enablers to responsive feeding for caregivers were identified in a systematic review of responsive feeding behaviours [18]. Barriers and enablers within five COM-B domains were identified: psychological capacity, physical and social opportunity, reflective and automatic motivation. For example, barriers to responsive feeding including not recognising developmental signs and feeding cues, having feeding goals, feeling stigmatised by HCP attitudes for formula feeding and also written instructions on formula opposing responsive feeding practices can discourage responsive feeding. Enablers such as caregivers being able to recognise infant feeding cues and being given advice and support from HCPs, family and peers were identified as facilitating responsive feeding. This systematic review identified the behaviours to target within an intervention to improve responsive infant feeding. It also highlighted the need for responsive feeding interventions for caregivers to be developed in tandem with guidance for HCPs. Such HCPs include midwives, health visitors and support workers such as family mentors who work with families to provide advice and support including around infant feeding.

Having established the evidence base for responsive feeding intervention development, the MRC Framework [23] further emphasises engaging and working with stakeholders at each stage of designing and conducting intervention research to maximise the likelihood that interventions are fit for purpose and have positive impacts on health outcomes. Therefore, the co-creation of interventions with caregivers and HCPs such as health visitors, infant feeding leads and support workers who work with caregivers and offer infant feeding advice and support is vital to support responsive feeding. The framework also highlights considering the implementation of the intervention during its development to increase the likelihood that the intervention can be effectively transferred into real-world settings.

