Caregivers seeking health information for their children have reported using the internet as their main source of information and reported high levels of confidence [25], and individuals seeking health information will most often use mobile devices [26]. However, a review of websites on infant health promotion including infant feeding found that the quality, accessibility and readability of the information was poor or adequate [27], highlighting the need for the development of interventions for caregivers and HCPs to be evidence-based, appropriate and useable.

The Public, Patient, Involvement and Engagement (PPIE) group who informed the development of this funding application suggested that any intervention around responsive feeding should utilise digital technology. Therefore, this research aims to develop an app to deliver a behaviour change intervention to caregivers. The chosen approach is a Reusable Learning Object (RLO) which consists of an interactive format with audio, text, animations and videos to promote health behaviour change. To this end, this research will co-create a RLO with caregivers to promote responsive feeding.

The aim of this study is to develop a RLO for caregivers of infants under one year to increase awareness, understanding and use of responsive infant feeding behaviours (CRIB). Improving responsive feeding will contribute to the prevention of obesity at an individual and population level. In addition, this study aims to develop infographic guidance for HCPs and support workers to use with caregivers alongside the RLO.

Objectives:To co-design a RLO to increase caregiver awareness, understanding and use of responsive infant feeding behaviours.To create an infographic for HCPs and support workers to improve their knowledge and ability to support caregivers with responsive feeding.To conduct an initial evaluation of the acceptability of the RLO for caregivers and the guidance infographic for HCPs and support workers.To determine the care pathways within the NHS, social care enterprises and the local authority where the RLO will be offered to caregivers with appropriate support.

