## Figures and Tables

**Figure 1 healthcare-12-00029-f001:**
[figure not shown]
Outline of study phases and components.

**Table 1 healthcare-12-00029-t001:** Potential RLO components, COM-B elements and TDF domains.

Topic Idea	COM-B Component	TDF Domain
How do I work with others to help me carry out responsive feeding?	Opportunity	Social influences
What can I change around me to improve my ability to responsive feed?	Capability	Behavioural regulation; Environment
What are the cues for hunger/fullness from my baby?	Capability	Knowledge/Skills
Why should I carry out responsive feeding?	Motivation	Goals/Intentions

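### Survey 2, items 2 and 3: both ask about cue-based feeding, but one comparator is ambiguous and the other does not apply to every caregiver

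*Protocol article*

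**What the plan says.** Section 2.3.4 gives Survey 2 the task of showing the RLO's impact on caregivers' behaviour around responsive feeding. The Analysis paragraph of that section says the closed questions will be tabulated for that purpose. Up to 30 caregivers will take part.

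The form has seven closed items with three responses: Agree, Neutral, Disagree. The two at issue are:

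- Item 2: "I am more likely to feed my baby based on their cues or signs than other ways for example, other people’s advice"
- Item 3: "I am more likely to feed my baby based on their cues or signs than other ways such as instructions on baby food tins"

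The Introduction supplies the behavioural model against which these can be read. It defines responsive feeding as infants giving clear cues and "their caregivers responding to these feeding cues promptly and in a developmentally appropriate way". Among the enablers it says that "being given advice and support from HCPs, family and peers were identified as facilitating responsive feeding". Among the barriers it says that "written instructions on formula opposing responsive feeding practices can discourage responsive feeding". Table 1 adds a planned RLO topic: "How do I work with others to help me carry out responsive feeding". The aim is to "develop a RLO for caregivers of infants under one year".

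**The concern.** An agreement item that contrasts A with B can be read only if B is clearly the thing the intervention is meant to displace, and if every respondent has some experience of B. Item 2 puts advice in the place of B without qualification, although the study treats good advice as part of the route to responsive feeding and is producing an infographic so that professionals can support caregivers. Item 3 names a product that differs from the one in the protocol's barrier and that some caregivers of infants under one will not use.

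At stake is how the frequencies for these two items are read. They come closest to a statement about what the caregiver will do, so a report on behaviour change will lean on them.

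**Working it through.** The plan gives no figure to reproduce, because Section 2.1 states that no sample size calculation was done. The check compares wording.

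**Step 1: which items concern feeding behaviour.** In Table A2, Part 2, items 1 and 6 ask about understanding, 4 and 5 about confidence, and 7 about motivation. Items 2 and 3 ask how the baby will be fed. That is 2 of 7.

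**Step 2: what an answer to item 2 can mean.** Consider three caregivers after using the RLO.

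- One used to follow a relative's fixed views and now follows cues. She answers Agree, and the answer is clear.
- One feeds by cues because a family mentor advised it. She may answer Agree, since she does feed by cues. She may also answer Neutral or Disagree, since she sees no opposition between the cues and the advice.
- One has not changed and still goes by what others tell her. She answers Neutral or Disagree.

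Neutral and Disagree can therefore hold both the third caregiver and some like the second. The form cannot tell them apart.

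**Step 3: what item 3 covers under each reading.**

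| Reading of the tin | Matches the formula barrier? | Does not apply to |
|---|---|---|
| Solid baby food | No | Infants on milk only |
| Formula milk | Yes, but loosely worded | Exclusively breastfed infants |

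Under both readings some caregivers must choose one of three answers about something they do not use.

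**Step 4: whether those answers can be separated afterwards.** Part 1 of Survey 2 records caregiver or public contributor status, whether the child is under one, involvement in RLO development, and an optional email address. It records neither feeding mode nor whether solids have started. Part 2 has no free-text item, unlike Survey 1. The surveys are anonymous. The answers cannot be separated.

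**Step 5: effect on a percentage.** With 30 respondents, one answer moves a percentage by 100/30 = 3.3 points. Let k respondents be those to whom item 3 does not apply, a of them answering Agree, and let A be the Agree answers from the others. The reported share is (A + a)/30. The share wanted is A/(30 − k). Reported minus wanted is positive if a/k exceeds A/(30 − k) and negative if it falls below. Neither k nor a can be found from the form or the document, so both the size and the direction of the error are unknown.

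**The case against.** The other side has a good deal of substance.

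- Both items ask about feeding by cues, which is the core of the protocol's definition. That stands: a reader might infer that the items do not measure responsive feeding at all, and the text does not support this.
- In both items the real comparator is other ways of feeding; advice and tins are only examples. A caregiver without a tin can still say whether she goes by cues. This softens the problem, but the example is the one concrete thing the respondent is given, and in item 3 it is the main difference from item 2.
- A caregiver advised to feed by cues may well answer Agree to item 2. That stands. A reader might infer that the item scores the intended pathway as failure, but it is ambiguous and not reversed. The Introduction also counts stigmatising professional attitudes as a barrier, so advice is not uniformly helpful, and advice that runs against cues would be a fair contrast. The item does not limit itself to that.
- The tins may have been meant as formula tins. If so, the fault is one of terminology, but the item still does not apply to exclusively breastfed infants.
- Items 4, 5 and 7 cover confidence and motivation, which the COM-B model treats as routes to behaviour. Two imperfect items do not undo the survey.
- The survey is exploratory and descriptive, and no threshold or decision is tied to these items. That limits the weight of the point. It does not remove the need for items that can be interpreted.

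**Conclusion.** The point holds as one of wording and response options. The comparator in item 2 is ambiguous against the protocol's own list of enablers. The comparator in item 3 does not match the stated barrier and does not apply to some respondents, who cannot be identified. The Agree, Neutral and Disagree percentages on these 2 of 7 items cannot be read cleanly as behaviour change.

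The number of respondents affected is not derivable. A reader might reason that solids start at six months, as in the recommendation cited in the Introduction, and that infant ages are evenly spread, giving 30 × 6/12 = 15 caregivers with no baby food tin, or 30 × 4/12 = 10 if solids start at four months. The document does not support either figure as an estimate. It gives no age or feeding-mode distribution for Survey 2, a recommendation is not a record of practice, and the calculation holds only if the tin contains solid food. Under the formula reading the relevant share is exclusively breastfed infants, which the document does not give.

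The change is worth making before the survey is sent out, because missing feeding information cannot be recovered from anonymous responses. It does not threaten the study.

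**What to change.** Four changes to the Survey 2 form and its analysis:

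1. Item 2: limit the comparator to a single non-responsive alternative, for example advice that goes against the baby's cues.
2. Item 3: replace the reference to tins with instructions on formula or baby food packaging.
3. Item 3: add a *Not applicable* response, and report percentages among those to whom the item applies, with that denominator shown.
4. Part 1: add one tick-box question on feeding mode and stage (breast, formula or combination; solids started or not), so that item 3 can be read by group.

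The cost is a minor amendment to one form, one extra question for respondents, and a slightly smaller denominator for item 3.
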